## Abstract

**Background:**

Lumbrokinase has been widely used for patients with acute ischemic stroke (AIS) in China; however, because rigorously designed studies are lacking, safety and efficacy of lumbrokinase in the treatment of acute ischemic stroke remains largely unknown. In this multicenter, randomized, and controlled trial, we aim to compare lumbrokinase plus aspirin versus aspirin alone in patients with acute ischemic stroke.

**Methods:**

A total of 220 eligible participants will be randomized to either the intervention or control group with a 1:1 ratio. These participants must be diagnosed with acute ischemic stroke for the first time, whose symptoms appear within 72 h. Their NIHSS score must be greater than 5 and less than 15, and their age must be between 35 and 85 years old. They must have not received intravenous thrombolysis, arterial thrombolysis, or intravascular intervention. Participants in the intervention group will be treated with lumbrokinase plus aspirin for the first 90 days. Participants in the control group will use placebo plus aspirin for the first 90 days. Then, all participants will be treated with aspirin only and followed up for another 90 days (180-day follow-up). The primary outcome is the modified Rankin Scale (mRS) score. The secondary outcomes are National Institutes of Health Stroke Scale (NIHSS) score, Activity of Daily Living (ADL) Scale score, coagulation function, and serum hypersensitive C-reactive protein. The exploratory outcomes are fasting lipid panel, recurrence rate, the occurrence of cardiovascular and cerebrovascular events, and the mortality rate. Safety evaluations include liver function and kidney function, serum fibrinogen, adverse events, serious adverse events, and bleeding events. Adherence of participants will also be assessed.

**Discussion:**

This trial will investigate the efficacy and safety of lumbrokinase plus aspirin as compared to aspirin alone in the treatment of acute ischemic stroke.

**Trial registration:**

Chinese Clinical Trial Registry, ChiCTR2000032952. Registered on May 16, 2020.

## Administrative information

Note: the numbers in curly brackets in this protocol refer to SPIRIT checklist item numbers. The order of the items has been modified to group similar items (see http://www.equator-network.org/reporting-guidelines/spirit-2013-statement-defining-standard-protocol-items-for-clinical-trials/).

## Introduction

### Background and rationale {6a}

Stroke is a major cause of mortality and morbidity worldwide. Each year, 15 million people are diagnosed with stroke globally; of them, 5 million suffer from death and another 5 million become permanently disabled [1]. Ischemic stroke accounts for approximately 80 to 87% of all strokes [2]. Among patients with a minor ischemic stroke or a transient ischemic attack (TIA), 3 to 15% will get ischemic stroke 90 days later [3]. As a traditional and the most widely used antiplatelet therapy, aspirin reduces the risk of early recurrent ischemic stroke and improves long-term outcomes without a risk of hemorrhagic complications. However, breakthrough ischemic strokes are not uncommon in patients who are already taking aspirin monotherapy and an addition of a second antiplatelet therapy like clopidogrel significantly increases the risk of bleeding.

In the current Chinese guidelines for the treatment of acute ischemic stroke (AIS), lumbrokinase is listed as a defibrinogenating agent with strong recommendation [4]. Lumbrokinase is extracted from special earthworms (*Lumbricus rubellus*) [5]. It is actually a name of a group of bioactive proteolytic enzymes including plasminogen activator and plasmin [6]. Unlike tissue plasminogen activator (t-PA), lumbrokinase does not have the side effects of excessive bleeding or heavy blood loss, although it converts plasminogen to plasmin and dissolves fibrin clots (Fig. 1) [7]. Lumbrokinase reduces fibrinogen, prolongs prothrombin time (PT) and activated partial thromboplastin time (APTT), reduces plasma viscosity, and inhibits platelet aggregation. In a meta-analysis of 4751 patients from 33 randomized controlled studies, You et al. found that lumbrokinase could facilitate the recovery of neurological functions and improve the activity of daily living, with mild side effects including nausea and vomiting, black stool (but stable hemoglobin levels), dizziness and other symptoms at a low frequency [8].

**Fig. 1 Fig1:**
[figure not shown]
How lumbrokinase works

A number of randomized clinical trials also investigated the effects of lumbrokinase plus aspirin for AIS. Zuo found that lumbrokinase plus aspirin decreased plasma fibrinogen concentration, whole blood viscosity and plasma viscosity. Patients treated with lumbrokinase plus aspirin had lower NIHSS scores 12 months later [9]. Similarly, Zhou et al. found that patients treated with lumbrokinase plus aspirin had better outcomes in quality of life per Bathel index and Chinese Stroke Scale (CSS). Nonetheless, the available studies were usually of poor quality with various methodological limitations. Thus, we aim to investigate the efficacy and safety of lumbrokinase plus aspirin as compared to aspirin alone in the treatment of AIS.

### Objectives {7}

We aim to investigate the efficacy and safety of lumbrokinase plus aspirin as compared to aspirin alone in the treatment of AIS.

The primary outcome is the Modified Rankin Scale (mRS) score.

The secondary outcomes are National Institutes of Health Stroke Scale (NIHSS) score, Activity of Daily Living (ADL) Scale score (Barthel index), coagulation function: prothrombin time (PT), activated partial thromboplastin time (APTT), serum fibrinogen (FIB) concentration, and serum hypersensitive C-reactive protein (hs-CRP).

### Trial design {8}

In this prospective, multicenter, randomized, double-blind, placebo-controlled clinical trial, lumbrokinase plus aspirin is compared to aspirin alone. We plan to enroll 220 participants with first time diagnosis of AIS. The participant allocation ratio is 1:1. Participants will be treated for the first 90 days. Then, all participants will be treated with aspirin only and followed up for another 90 days (180-day follow-up). A flowchart of the study is shown in Fig. 2. Central ethical approval of LUCENT has been confirmed by the Ethics Committee of Dongzhimen Hospital, Beijing University of Chinese Medicine (No.DZMEC-KY-2019-202). This trial will be conducted in adherence to the Declaration of Helsinki. Informed consent will be obtained from all participants or their legal representative, in writing, before inclusion in the trial. The trial has been registered in the Chinese Clinical Trial Registry (ChiCTR2000032952).

**Fig. 2 Fig2:**
[figure not shown]
The flow diagram of this trial. PO, per os; AIS, acute ischemic stroke

## Methods: participants, interventions, and outcomes

### Study setting {9}

LUCENT will be conducted in ten hospitals across China from June 2020 to April 2022. They are Dongzhimen Hospital, Beijing University of Chinese Medicine, Dongfang Hospital, Beijing University of Chinese Medicine, Beijing University of Chinese Medicine Third Affiliated Hospital, Xuanwu Hospital Affiliated to Capital Medical University, the First Teaching Hospital of Tianjin University of TCM, Second Affiliated Hospital of Tianjin University of TCM, Tianjin Huanhu Hospital, Affiliated Hospital of Jiangxi University of Traditional Chinese Medicine, the First Affiliated Hospital of Nanchang University, the Second Affiliated Hospital of Nanchang University.

### Eligibility criteria {10}

The diagnosis of AIS in this trial is based on the guidelines from the Chinese Society of Neurology [10]. Participants are considered for inclusion if they meet the criteria as defined below.
Participant is diagnosed with acute ischemic stroke for the first timeSymptoms of acute ischemic stroke appear within 72 hBefore the onset of symptoms of acute ischemic stroke, the mRS score of the participant is less than or equal to 2Participant has not received intravenous thrombolysis, arterial thrombolysis, or intravascular interventionThe participant’s NIHSS score is greater than 5 and less than 15The age of the participant is between 35 and 85 years oldAgree to participate in the trial and signed informed consent form

Exclusion criteria are as follows:
The participant has a hemorrhagic cerebrovascular disease (including subarachnoid hemorrhage, cerebral hemorrhage, and other intracranial hemorrhage)Transient ischaemic attack (TIA) and silent cerebral infarctionKnown or suspicion for cardiogenic embolism: atrial fibrillation, dilated cardiomyopathy, infective endocarditis, mitral valve prolapse, sick sinus syndrome, atrial myxoma, patent foramen ovale, atrial septal defect, ventricular wall aneurysm, etc.Carotid artery stenosis ≥70%Blood pressure exceeds 180/100 mmHg (24/13.3 kPa) after active drug treatmentBlood homocysteine exceeds 20 μ mol/L after active drug treatmentUsed defibrase within 24 h (including urokinase, snake venom preparation, batroxobin, lumbrokinase, etc.)Have the following serious complications:Cardiac insufficiency: myocardial infarction, acute heart failureHepatic insufficiency: total bilirubin>3 mg/dL, albumin<3 g/dL, ALT or AST increased to 3 times or more than the normal upper limit (≥120 IU/mL)Renal insufficiency: creatinine>178 μmol/L (2 mg/dL), urea nitrogen>18 mmol/L (40 mg/dL)(9)Participant with bleeding tendencies (active gastric ulcers or bleeding) or hemorrhagic diseases or severe bleeding within 3 months, such as hemoptysis, hematochezia (fecal occult blood test), thrombocytopenic purpura, coagulopathy with INR > 1.7, active tuberculosis, etc., including platelet count<100 × 10^9^/L(10)Participant has already taken anticoagulants or antiplatelet drugs or nonsteroidal anti-inflammatory drugs within 7 days prior to the stroke event(11)Participant is allergic or intolerant to lumbrokinase or aspirin(12)Participant with dysphagia and could not be given drugs orally(13)Participant with a history of malignant tumor or aneurysm (including intracranial aneurysm or peripheral aneurysm)(14)Women with recent pregnancy plans, as well as pregnant and lactating women(15)Participant who had a surgery in the last 7 days(16)Participant has a major mental illness and could not control his/her own actions, unable to cooperate with the trial(17)Participant who is unable to understand the informed consent form or is unwilling to provide personal information or does not want to enter the trial(18)Participant who participated in another clinical trial in the last 30 days

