### Who will take informed consent? {26a}

Patients with AIS will be screened for eligibility to participate in this trial based on the abovementioned criteria. After the patient has been assessed as eligible by the treating physician, he/she will receive initial study information. Within 72 h, patients are invited to meet with the research physician to discuss any remaining questions and sign the informed consent.

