**Liver function and kidney function**							
ALT	X		X	X	X	X	
AST	X		X	X	X	X	
TBil	X		X	X	X	X	
BUN	X		X	X	X	X	
Scr	X		X	X	X	X	

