## Trial status

Recruiting started in September 2020. The current protocol is version 2 of 28-12-2019. Currently (29th of November 2021), we have recruited 46 participants. Participant recruitment is estimated to be completed around August 2022.

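### The urea nitrogen exclusion limit and its bracketed equivalent differ by 26%: 18 mmol/L is 50.4 mg/dL, not 40 mg/dL (minor)

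*Protocol article*

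**What the plan says.** Exclusion criterion 8 of the protocol article (Eligibility criteria {10}) lists serious complications. Under renal insufficiency it gives two laboratory limits, each in SI units with a conventional-unit figure in brackets: "creatinine>178 μmol/L (2 mg/dL") and "urea nitrogen>18 mmol/L (40 mg/dL"). Only a comma separates them, and the text does not say whether either one excludes or both are needed. The blood pressure criterion in the same list is also given in two units: "Blood pressure exceeds 180/100 mmHg (24/13.3 kPa").

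The criterion is meant to be applied. Under Who will take informed consent? {26a} the article states: "Patients with AIS will be screened for eligibility to participate in this trial based on the abovementioned criteria". In Table 1 the block "Liver function and kidney function" marks blood urea nitrogen at the screening visit. No other section gives a urea nitrogen limit or says which unit governs.

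**The concern.** The bracket should restate the leading figure in another unit, but it states a different concentration. The criterion therefore carries two limits, and the bracketed one is the stricter. A candidate whose urea nitrogen lies between them passes on the SI figure and fails on the bracketed one. Ten hospitals apply the list, so each limit in it should have a single meaning.

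What is at stake is who enters the trial on this one criterion. If the higher limit was intended, a site using the bracket would turn away eligible patients. If the lower limit was intended, a site using the SI figure could enrol patients who should have been excluded.

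**Working it through.** **Inputs.** From Eligibility criteria {10}: urea nitrogen 18 mmol/L with 40 mg/dL; creatinine 178 μmol/L with 2 mg/dL; blood pressure 180/100 mmHg with 24/13.3 kPa. The conversion constants are physical constants, not figures from the article: nitrogen 14.007 g/mol, urea 60.06 g/mol, creatinine 113.12 g/mol, and 0.133322 kPa per mmHg.

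**Formula.** mg/dL = mmol/L × (g/mol) / 10. A urea molecule holds two nitrogen atoms, so urea nitrogen is 2 × 14.007 = 28.014 g/mol and the factor is 2.8014.

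**Attempt to reproduce the printed pair.**
- 18 mmol/L × 2.8014 = 50.43 mg/dL, against 40 printed.
- 40 mg/dL / 2.8014 = 14.28 mmol/L, against 18 printed.
- Ratio: 18 / 14.28 = 1.26. Equivalently, 40 is 1 − 40/50.43 = 21% below the correct bracket.
- The printed pair implies a factor of 40 / 18 = 2.22.

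**Could another reading of the analyte explain it?**

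| Reading | Factor | 18 mmol/L is | 40 mg/dL is |
|---|---|---|---|
| Urea nitrogen (two N) | 2.8014 | 50.4 mg/dL | 14.3 mmol/L |
| Whole urea | 6.006 | 108.1 mg/dL | 6.66 mmol/L |
| Single nitrogen atom | 1.4007 | 25.2 mg/dL | 28.6 mmol/L |

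No reading gives a factor near 2.22.

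**Could rounding explain it?** If 40 were rounded to the nearest 10 mg/dL, it would stand for 35 to 45 mg/dL. That is 35/2.8014 = 12.5 to 45/2.8014 = 16.1 mmol/L, which does not reach 18.

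**Are brackets in this list true restatements elsewhere?**
- Creatinine: 2 mg/dL = 20 mg/L; 20 / 113.12 = 0.1768 mmol/L = 176.8 μmol/L, against 178 printed (0.7% apart).
- Blood pressure: 180 × 0.133322 = 24.0 kPa and 100 × 0.133322 = 13.3 kPa, as printed.

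Both convert correctly, so a bracket after such a limit is a conversion and not a second rule. The urea nitrogen bracket is the one that fails.

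**Band between the two limits.** Above 14.3 and up to 18 mmol/L: 18 − 14.28 = 3.72 mmol/L wide, or 50.43 − 40 = 10.43 mg/dL.

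**The case against.** The strongest reply is that the text already has a natural reading. The inequality sign sits on 18 mmol/L and the figure in brackets merely restates it, exactly as with creatinine. A site that works in mmol/L would never need the bracket. This stands: 18 mmol/L should be taken as the default. It does not make the bracket right, and the article nowhere says that the SI figure governs.

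A second reply is that safeguards exist. The article says that laboratory reference values are harmonised across hospitals before the start (Plans for assessment and collection of outcomes {18a}) and that monitors check compliance with the protocol (Frequency and plans for auditing trial conduct {23}). These may make divergent handling less likely, but neither tells a site which cut-off to use.

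A third is that this may be a clerical slip confined to the article, with the limit correct in the full protocol. That is possible. The hepatic limit just above has what looks like a unit slip of its own, "3 times or more than the normal upper limit (≥120 IU/mL"), where IU/L is presumably meant. It is harmless because the multiple of the upper limit beside it does the work. The urea nitrogen limit has no such companion rule, so the slip there leaves two competing numbers.

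A reader might also infer more than the article supports:
- **That ineligible patients were enrolled, or eligible ones turned away.** Nothing shows that any site used the bracketed figure or that any candidate fell in the band.
- **That the number recruited caps the damage.** The article reports "Currently (29th of November 2021), we have recruited 46 participants". This is everyone enrolled at that date, not a count of affected patients, and it misses anyone wrongly screened out.
- **That only patients with acceptable creatinine are concerned.** This assumes that the two renal limits are joined by *or*. If both were required, the band would matter only for patients with creatinine above 178 μmol/L. The text does not say which applies.

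**Conclusion.** The point holds as a minor error. The two figures in the urea nitrogen limit differ by 26%, and no rounding or alternative reading of the analyte reconciles them. The format makes >18 mmol/L the natural operative limit, so the most likely error is in the bracket. The article alone cannot confirm that.

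The consequence is limited to eligibility in the band above 14.3 and up to 18 mmol/L. It exists whether the creatinine and urea nitrogen limits are alternatives or joint conditions; only the set of patients to whom it applies changes. Power and the between-arm comparison are not affected, and the article gives no basis for estimating how many patients, if any, were handled differently. The conclusion rests only on the standard molar mass of urea nitrogen and on the bracket being meant as a conversion, which the neighbouring pairs support.

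**What to change.** Confirm the intended limit against the full protocol, which the article identifies under Trial status: "The current protocol is version 2 of 28-12-2019". Then print one consistent pair:
- by default, >18 mmol/L (50 mg/dL);
- if the lower limit was intended, >14.3 mmol/L (40 mg/dL).

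State in the same line whether the creatinine and urea nitrogen limits are joined by *or* or *and*. The hepatic unit label can be corrected in the same edit.

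The cost is one corrected figure and a connecting word, with no new tests or visits. Only if the lower limit was intended is there further work: looking up the screening blood urea nitrogen already recorded for enrolled participants, 46 at the status date plus any enrolled since.

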### Who will take informed consent? {26a}

Patients with AIS will be screened for eligibility to participate in this trial based on the abovementioned criteria. After the patient has been assessed as eligible by the treating physician, he/she will receive initial study information. Within 72 h, patients are invited to meet with the research physician to discuss any remaining questions and sign the informed consent.

### Additional consent provisions for collection and use of participant data and biological specimens {26b}

The collection and use of participants’ data will be stated in the informed consent. We will not collect biological specimens. There will be no additional consent provisions.

## Interventions

### Intervention description {11a}

Participants in both groups will receive standard medical care including aspirin 100 mg daily throughout the trial. Besides, participants in the intervention group will be treated with oral lumbrokinase (600,000 units), three times a day, half an hour before each meal plus oral aspirin 100 mg, once a day. Participants in the control group will be treated with placebo plus aspirin at a similar schedule. The course of treatment is 90 days with a follow-up period till day 180; after 90 days, all participants will continue the same aspirin treatment. An overview of data collection schedule is shown in Table 1. Additional medication use, adverse events (AEs), and serious adverse events (SAEs) will be recorded throughout the trial.

**Table 1 Tab1:** Outcome evaluation time points

Time	Screening period	Baseline stage	Period of drug treatment(90d)				Follow-up
	− 72 h	D0	D14 ± 3 days	D28 ± 3 days	D60 ± 3 days	D90 ± 3 days	D180 ± 7 days
Visit date	X	X	X	X	X	X	X
Inclusion/exclusion criteria	X						
Informed consent	X						
Demographic data	X						
Vital signs and physical examination	X	X	X	X	X	X	
History of malignant tumor and aneurysm	X						
Family history, medical history and treatment history of TIA, Stroke, hemorrhagic disease	X						
Previous history of disease	X						
Allergic history	X						
History of tobacco and alcohol		X					
**Routine blood**							
RBC		X				X	
WBC		X				X	
Neutrophil		X				X	
Lymphocyte		X				X	
PLT		X				X	
Hb		X				X	
PCV		X				X	
**Urinalysis**							
U-LEU		X	X	X	X	X	
U-BLD		X	X	X	X	X	
R-PRO		X	X	X	X	X	
U-Ket		X	X	X	X	X	
**Routine stool**							
OB	X					X	
**Liver function and kidney function**							
ALT	X		X	X	X	X	
AST	X		X	X	X	X	
TBil	X		X	X	X	X	
BUN	X		X	X	X	X	
Scr	X		X	X	X	X	
**Fasting lipid panel**							
TC		X				X	
TG		X				X	
HDL		X				X	
LDL		X				X	
Fasting blood glucose		X				X	
**Coagulation function**							
PT		X	X	X	X	X	
APTT		X	X	X	X	X	
FIB		X	X	X	X	X	
hs-CRP		X				X	
Homocysteine	X						
ECG	X					X	
MRI of brain	X					X	
ADL scale (BI)		X				X	X
NIHSS	X		X	X	X	X	
mRS before stroke	X						
mRS		X	X	X	X	X	X
Recurrence rate			X	X	X	X	X
Cardiovascular and cerebrovascular events			X	X	X	X	X
Bleeding event			X	X	X	X	
Mortality rate			X	X	X	X	X
AE and SAE		X	X	X	X	X	
Combined use of drugs		X	X	X	X	X	
Adherence evaluation			X	X	X	X	

Abbreviations: *TIA*, transient ischaemic attack; *RBC*, erythrocyte count; *WBC*, leukocyte count; *PLT*, blood platelet; *Hb*, hemoglobin; *PCV*, packed cell volume; *U-LEU*, urine leukocyte; *U-BLD*, urine latent blood; *R-PRO*, urine protein; *U-Ket*, urine ketone bodies; *OB*, fecal occult blood; *ALT*, alanine aminotransferase; *AST*, aspartate aminotransferase; *TBil*, total bilirubin; *BUN*, blood urea nitrogen; *Scr*, serum creatinine; *TC*, total cholesterol; *TG*, triglyceride; *HDL*, high-density lipoprotein; *LDL*, low-density lipoprotein; *PT*, prothrombin time; *APTT*, activated partial thromboplastin time; *FIB*, fibrinogen; *hs-CRP*, hypersensitive C-reactive protein; *ECG*, electrocardiogram; *MRI*, magnetic resonance imaging; *ADL*, activity of daily living; *BI*, Barthel Index; *NIHSS*, National Institutes of Health Stroke Scale; *mRS*, Modified Rankin Scale; *AE*, adverse event; *SAE*, serious adverse event

### Explanation for the choice of comparators {6b}

For patients with acute ischemic stroke who do not conform to the indications of intravenous thrombolysis or intravascular thrombectomy, and have no contraindications, oral aspirin should be given as soon as possible after onset in China [4]. Aspirin can be changed to a prophylactic dose after the acute phase. So its selection as comparator is justified. In this trial, aspirin will be taken 100 mg once a day for 180 days. Its dose, frequency, and days are in accordance with the current practice in China. The side effects of aspirin in the drug instruction include the following: (1) Upper and lower gastrointestinal discomfort, such as indigestion, gastrointestinal, and abdominal pain; rash, urticaria, edema, and pruritus; cardiovascular and respiratory system discomfort. (2) Rare cases included gastrointestinal inflammation and gastroduodenal ulcers. (3) Very rarely, there may be gastrointestinal bleeding and perforation, hematoma, epistaxis, urinary genital bleeding, and gingival bleeding. (4) Particularly rarely, gastrointestinal bleeding, intracerebral hemorrhage, anaphylactic shock, and transient liver damage with elevated liver transaminase. (5) Dizziness and tinnitus were reported during drug overdoses. Nevertheless, the benefits of aspirin in patients with ischemic stroke outweigh the side effects, which is internationally recognized. In this trial, participants’ adverse events will be closely observed and treated in time.

